### Sample size and expected enrolment

The registry is designed for indefinite, continuous enrollment. We distinguish two enrollment streams: incident cases (children newly diagnosed with HD or ARM presenting to COCOE, estimated at a minimum of 5 per month) and previous cases (patients previously diagnosed but lost to follow-up and re-engaged, estimated at approximately 3 per month). Combined, the registry aims to enroll approximately 96 participants per year. Based on a prevalent backlog of an estimated 150–200 patients currently followed at COCOE, total enrollment over 5 years is projected at 480–680 participants.

While no minimum sample size is required for registry operation, we provide a feasibility projection. Based on published ARM cohort data reporting approximately 24–30% achieving full fecal continence [14], and HD cohort data reporting approximately 39% achieving a BFS ≥ 17 by adolescence, we project a combined continence event rate of approximately 30–35% within the first 5 years of registry operation [21]. This corresponds to approximately 145–240 continence events across the projected 480–680 enrolees, supporting inclusion of up to 14–24 covariates in the primary Cox model at an events-per-variable (EPV) threshold of 10 [22]. Importantly, this time-to-event framing includes all enrolled participants regardless of age at enrollment, resolving the limitation of the age-5 cross-sectional design by allowing older prevalent cases to contribute person-time and events from their enrolment date. Pre-specified multivariable analyses will be triggered only once this EPV threshold is confirmed at interim review; otherwise analyses will be limited to descriptive and unadjusted comparisons.

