### Catchment and representativeness

The Montreal Children’s Hospital is one of two paediatric tertiary care centres in Québec and receives colorectal referrals from across the province, including from Nunavik and the Cree territory of James Bay, as well as selected complex referrals from other provinces. The registry therefore captures a substantial proportion, but not the entirety, of the incident paediatric HD and ARM population in Québec. To quantify representativeness rather than assert it, the age, sex, diagnosis and severity distribution of enrolled participants will be compared at each annual analysis against two external benchmarks: (i) expected provincial case counts, derived by applying published Canadian incidence estimates for HD (2.05 per 10,000 live births [1]) and ARM (approximately 1 in 2,162 births [3,4]) to Québec live-birth denominators; and (ii) the published case-mix of the ARM-Net and PCPLC registries [11,13]. Aggregate, non-identifying information on patients who are approached but decline enrollment (age band, diagnosis, and referral region) will also be recorded so that a non-participation comparison can be reported. Any material divergence, for example under-representation of remote communities or of the most severe Krickenbeck categories, will be reported explicitly alongside registry outputs and taken into account when interpreting external validity.

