### Outcome measures

The primary outcome and its definition are described in detail below. Pre-specified secondary outcomes are presented in Table 2 below, each with its definition, instrument or data source, timing of ascertainment, and analytic role.

**Table 2 pone.0356813.t002:** Pre-specified primary and secondary outcomes.

Outcome	Definition	Instrument / Data Source	Timing of Ascertainment	Priority	Analytic Role
**Time to fecal continence**	First clinic visit (confirmed at subsequent visit) at which the participant meets social continence threshold: BCS criteria (ARM) or BFS ≥ 17 (HD), from date of definitive repair	BCS (ARM) [16] or BFS (HD) [17], parent/caregiver proxy to age 11; self-report from age 12	Annual visits from age 3	**PRIMARY**	Kaplan–Meier estimation; Cox proportional hazards regression; Fine-Gray model for competing risks; landmark analyses at ages 5 and 10
HD-associated enterocolitis (HAEC)	≥1 physician-confirmed episode meeting Ruttenstock criteria requiring medical treatment	Clinical record review; REDCap adverse event log	Each annual visit; first episode date recorded	Secondary 1	Cox regression / Fine-Gray competing risks; descriptive incidence rate
Reoperation rate	Any unplanned surgical return to the operating room following index repair	Operative report review; REDCap surgical procedure log	Cumulative from index repair; each annual visit	Secondary 2	Cox regression / Fine-Gray competing risks; cumulative incidence curve
Disease-specific quality of life	HAQL total score and subscale scores (age-appropriate version)	HAQL questionnaire, self- or proxy-report [18]	Ages 6, 10, and 14 years	Secondary 3	Linear mixed-effects model (repeated measures); descriptive means by group
Transition readiness	Transition Readiness Assessment Questionnaire	TRAQ [19], self-report	Ages 14 and 17 years	Secondary 4	Linear mixed-effects model; descriptive score trajectory
Loss to follow-up (LTFU)	No clinic encounter, survey, or successful contact for ≥18 months while under age 18 and not yet transitioned	REDCap contact log; clinic attendance record	Flagged at 18-month mark; reviewed at each annual analysis	Secondary 5	Logistic regression (ever-lost vs retained); descriptive LTFU rate

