The primary outcome is time to achievement of fecal continence from the date of definitive surgical repair, analysed as a time-to-event outcome. For participants with ARM, continence is assessed using the Baylor Continence Scale (BCS) [16], with social continence defined as no soiling episodes in the preceding 4 weeks per published BCS criteria, completed by the parent or caregiver proxy up to age 11 and by self-report from age 12. For participants with HD, continence is assessed using the Bowel Function Score (BFS) [17], with social continence defined as a BFS score ≥ 17, administered to the parent or caregiver proxy up to age 11 and by self-report from age 12. Both instruments are administered at every annual clinic visit beginning at age 3 years. The earliest clinically meaningful assessment for continence is age 3, consistent with normal developmental milestones for voluntary bowel control. Participants will be censored at age 18, death, transition to adult care, or loss to follow-up, whichever occurs first.

Pre-specified secondary outcomes, listed in priority order, are: (1) Hirschsprung-associated enterocolitis (HAEC), defined as at least one physician-confirmed episode meeting the Ruttenstock diagnostic criteria and requiring medical treatment, assessed at each annual visit [20]; (2) reoperation rate, defined as any unplanned surgical return to the operating room following index repair, assessed cumulatively; (3) disease-specific quality of life, measured using the HAQL [18] at ages 6, 10, and 14 years using age-appropriate versions; (4) transition readiness, assessed at ages 14 and 17 years using the validated Transition Readiness Assessment Questionnaire (TRAQ) [19], and (5) loss to follow-up rate, defined operationally in the Loss to Follow-Up section. Each secondary outcome will be reported descriptively and, where the events-per-variable threshold is met (see Sample Size section), included as an endpoint in pre-specified multivariable analyses with the analytic role specified in the Statistical Analysis section.

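### The projected 145–240 continence events in 5 years are not supported by the protocol's own event definition and enrolment inputs

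*Protocol article*

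**What the plan says.** All places are in the protocol article.

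- **Enrolment** (Sample size and expected enrolment). There are two streams: "children newly diagnosed with HD or ARM presenting to COCOE, estimated at a minimum of 5 per month" and "patients previously diagnosed but lost to follow-up and re-engaged, estimated at approximately 3 per month". Together these streams are expected to bring in about 96 children a year. The 5-year total of 480–680 is said to rest on a backlog of 150–200 patients already followed at the centre.
- **Rate** (same section). ARM cohorts reach 24–30%, with no time horizon given. The other source is "HD cohort data reporting approximately 39% achieving a BFS ≥ 17 by adolescence". These are merged into 30–35% within the registry's first 5 years.
- **Events** (same section). "This corresponds to approximately 145–240 continence events across the projected 480–680 enrolees". This is said to support 14–24 covariates in the primary Cox model at 10 events per variable (EPV).
- **Event definition** (Outcome measures, Table 2). "First clinic visit (confirmed at subsequent visit) at which the participant meets social continence threshold".
- **Assessment schedule** (Outcome measures). "Both instruments are administered at every annual clinic visit beginning at age 3 years".
- **Models** (Statistical analysis, Objective 3; Strengths and limitations). ARM and HD are modelled separately, EPV is judged within each disease, and HD is described as the smaller cohort.

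**The concern.** An end-state proportion is used as a 5-year incidence. Children who enter in infancy after roughly the first year count in full in the projection, yet under annual assessment from age 3 with later confirmation they cannot supply a confirmed event by year 5. They make up a large part of the incident stream, which is itself the largest stream.

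This is the only feasibility figure given for the primary outcome. The covariate count is taken straight from it. The Year 3 interim and the Year 4–5 report of all multivariable analyses are plausible only if events arrive at about this pace. A child enrolled near birth is at most 3 years old at Year 3, so that interim, which is limited to participants who have reached age 5, would draw on prevalent and late-diagnosed children only.

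**Working it through.** **1. The plan's figure reproduces.** 480 × 0.30 = 144 and 680 × 0.35 = 238, rounded to 145–240. Divided by 10, this gives 14–24 covariates. The multiplication is correct; the question is what goes into it.

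**2. Enrolment.** (5 + 3) × 12 = 96 a year, and 96 × 5 = 480 with no backlog. Adding 150–200 gives 630–680. The upper bound contains the whole backlog and the lower bound none.

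**3. Combined rate.** With HD share w, rate = 0.39w + ARM rate × (1 − w).
- For 35% with ARM at 30%: w = 0.05/0.09 = 56%. With ARM at 24%: w = 0.11/0.15 = 73%.
- At 50/50 the rate is 31.5–34.5%.
- At the protocol's own incidences (HD 2.05 and ARM 4.63 per 10,000, so w = 30.7%) it is 28.6–32.8%.

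**4. Children able to have a confirmed event by year 5.** Assumptions, none stated in the protocol: incident cases enter near birth; re-engaged and backlog cases are aged 3 or over; the backlog is fully enrolled by year 4; confirmation takes one year; accrual is even; there is no dropout.
- Incident: 60 a year, 300 in all. Only year-1 entrants reach age 4 in time: 60.
- Re-engaged: 36 a year, 180 in all. Entrants in years 1–4 can be confirmed: 144.
- Backlog: 150–200.
- Total: 60 + 144 + 150 = 354, up to 404. With no backlog: 204.

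Events at the protocol's own 30–35%:

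| Scenario | Children able to have an event | Events | Share needed for 145 | Share needed for 240 |
|---|---|---|---|---|
| Backlog 150 | 354 | 106–124 | 41% | 68% |
| Backlog 200 | 404 | 121–141 | 36% | 59% |
| No backlog | 204 | 61–71 | 71% | not possible |

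**5. More generous readings, one at a time.**
- *Confirmation almost at once.* Incident entrants of years 1–2 (120), all 180 re-engaged and 150–200 backlog give 450–500 children: 450 × 0.30 = 135 to 500 × 0.35 = 175 events.
- *Late diagnosis.* Ages and entry times were simulated with one-year confirmation, late-diagnosed and prevalent ages uniform over 0–17, and a backlog of 200 entering over two years. If 30% of incident cases are diagnosed late, about 441 children qualify (up to 154 events); if 50%, about 473 (up to 165).
- *The upper bound.* 240/0.35 = 686 children, more than the 680 projected in total. Even 238 requires every enrolee to be assessable and confirmable within 5 years.

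**6. By disease (illustration).** Using the incidence mix of 30.7% HD and the protocol's disease-specific rates:
- HD: the 680 scenario implies 680 × 0.307 × 0.39 ≈ 81 events; 354–404 children imply about 42–48.
- ARM: the 680 scenario implies 680 × 0.693 × (0.24 to 0.30) ≈ 113–141; 354–404 children imply about 59–84.

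Each model has five candidate predictors. Counted as variables, they need 50 events. Counted as parameters, with deprivation entered as one linear term and sex as binary, HD needs 3 (four aganglionosis categories) + 4 = 7, or 70 events. ARM needs 6 (seven Krickenbeck groups) + 4 = 10, or 100 events. On parameters, both models clear EPV 10 under the stated projection and neither does under the base case. On variables, ARM clears it and HD falls just short.

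**The case against.** **The stated range is not impossible.** A reader might infer that 145–240 events cannot occur. The documents do not support that. The protocol says newly diagnosed, not newborn, admits ages 0–17 and gives no age-at-entry distribution. Table 2 asks for confirmation at a later visit without fixing the gap at 12 months, and the survey administration section prioritises the continence scales at each visit. The generous readings overlap the stated lower bound, and 141 against an approximate 145 is not a meaningful gap. What fails is the upper bound, and the support for the range as a whole.

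**61–71 is not the best estimate.** It applies only if no backlog is enrolled, which is what 480 implies taken literally. The 480 can be read as a cautious floor. However, the text bases the total on the backlog, and the Year 1 milestone expects at least a quarter of it: 480 + 0.25 × 150 ≈ 518.

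**The 35% is only slightly off.** A near-even mix gives 34.5%, which is close to an approximate 35%, and referral case-mix need not follow population incidence. This stands: 680 × 0.345 = 235 against 238. The time horizon matters far more.

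**Incidence.** One might argue that 60 incident cases a year exceed the whole province. At 6.68 per 10,000, 60 cases need about 89,900 births with full capture, while the centre "captures a substantial proportion, but not the entirety, of the incident paediatric HD and ARM population in Québec". But no birth count is given. At an assumed 70,000–90,000 births the province yields 47–60 cases, and out-of-province referrals and late diagnoses add to that. This is supporting evidence only.

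**No wrong analysis is forced.** Adjusted models are triggered by observed events within each disease, the interim is conditional, milestone dates are open to revision, and no minimum sample size is claimed. This stands and limits the severity.

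**Conclusion.** The projection is optimistic and does not follow from the protocol's own event definition. Under the working assumptions the expected count is about 106–141 confirmed events in 5 years, supporting about 10–14 parameters across both diseases together and fewer in each separate model. Either generous reading alone gives at most about 155–175; 240 is not reachable at the stated rates.

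The result depends on age at entry, backlog uptake and the confirmation interval, none of which the protocol quantifies. It allows for no dropout, nor for the expected 70–80% instrument completion per visit, although an event needs two completed assessments. Children already continent at entry, if not counted as new events, would lower every figure.

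Two inputs also conflict: a total based on the backlog whose floor omits it, and a rate needing an HD share of at least 56% beside a smaller HD cohort. The single primary Cox model behind the covariate count contradicts the separate-model plan. This should be fixed, but the EPV trigger means that it does not by itself invalidate any planned analysis.

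**What to change.** Restate the section on sample size and expected enrolment:

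1. Build enrolment by stream (incident, re-engaged, backlog) and age at entry, with assumed backlog uptake stated in both bounds. Full uptake gives 630–680.
2. Apply the event probability only to children who can have two assessments at age 3 or older before the data cut and who are not already continent at entry. State the confirmation interval.
3. Give expected events and supportable parameters separately for HD and ARM, each with its own rate, time horizon and assumed share of enrolment. Remove the pooled 14–24 covariate statement.
4. Align the Year 3 to Year 5 milestones with when those counts are expected.

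The registry is already enrolling, so observed entry ages and monthly counts could replace several assumptions. The cost is a recalculation and less favourable published figures; no additional participants or data collection are needed.

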### Social determinants of health

(a) Individual-level variables, collected directly from participants and caregivers using Statistics Canada standard wording [30]: sex assigned at birth (male, female, intersex); gender identity (man/boy, woman/girl, non-binary, another gender identity, prefer not to answer); race/ethnicity (self-identified, using Statistics Canada visible minority and Indigenous identity categories); household income before taxes (six categories: < $20,000; $20,000–$39,999; $40,000–$59,999; $60,000–$79,999; $80,000–$99,999; ≥ $100,000, aligned with Low Income Measure thresholds for Québec); highest level of education completed by the primary caregiver (less than high school diploma; high school diploma or equivalent; post-secondary certificate or diploma; bachelor's degree; graduate or professional degree); and employment status of the primary caregiver. For all individual-level SDOH variables, a “prefer not to answer” option will be provided and treated as missing in analyses, with missingness described and addressed using the plan detailed in the Statistical Analysis section.(b) Area-level deprivation, derived from the Pampalon Material and Social Deprivation Index (MSDI), 2021 census-based [31], linked to participant residence via the first three characters of the postal code (forward sortation area, FSA) using the Statistics Canada Postal Code Conversion File. Material deprivation (a composite of employment, income, and education) and social deprivation (a composite of living alone, separated/widowed/divorced status, and lone-parent status) will be treated as separate dimensions and analysed as quintile scores (Q1 = least deprived to Q5 = most deprived). [32] The FSA will not appear in any publication output.

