**Objective 3:** Factors associated with key outcomes. Time to achievement of fecal continence will be estimated using the Kaplan–Meier method, with curves reported separately for ARM and HD given the use of disease-specific instruments. Given the embryological, surgical, and prognostic distinctions between the two conditions, and the use of disease-specific continence instruments, multivariable analyses will be conducted separately for ARM and HD rather than as a single combined model. For each disease cohort, a Cox proportional hazards model will be fitted with disease-appropriate pre-specified candidate predictors: for ARM, Krickenbeck category, age at index repair, sex, syndromic status, and area-level deprivation quintile; for HD, length of aganglionosis, age at index repair, sex, syndromic status, and area-level deprivation quintile. The proportional hazards assumption will be tested for each model using Schoenfeld residuals. Where competing risks are present (death or transition prior to the continence event), the Fine-Gray subdistribution hazard model will be applied within each cohort. Pre-specified landmark analyses will report the proportions achieving continence by age 5 and age 10 for each disease, to allow benchmarking against published ARM and HD cohort data. For each disease-specific model, multivariable Cox regression will be triggered only once the events-per-variable (EPV) threshold of 10 is met within that cohort at interim review; otherwise analyses for that cohort will be limited to descriptive and unadjusted comparisons.

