Combining HD and ARM within a single registry carries both operational and analytic risks. Operationally, the two cohorts share only part of the data model. Shared elements (demographics, social determinants of health, health service utilisation, PedsQL modules, PECI, PREOM-BMP, TRAQ, and the loss-to-follow-up definition) are captured on common forms, while disease-specific elements (Krickenbeck classification and the BCS for ARM; length of aganglionosis, HAEC ascertainment, and the BFS for HD) are captured on separate branching instruments, so that no clinician or abstractor is presented with a field that does not apply to the patient in front of them. Analytically, the two cohorts are never pooled for primary, survival, or multivariable analysis, and the events-per-variable threshold is assessed within each cohort separately. This is a conservative choice that may delay adjusted analyses in the smaller HD cohort. Pooling is confined to descriptive summaries of registry-level metrics such as enrollment, data completeness, and loss to follow-up, where disease group will always be reported as a stratifying variable. The main residual risk is therefore loss of statistical efficiency rather than confounding, and it is accepted in preference to a single combined model whose coefficients would be difficult to interpret clinically.

Finally, the primary outcome relies on instruments administered by proxy in younger children and by self-report from age 12, so the change of respondent within an individual’s follow-up may introduce measurement discontinuity. Respondent type will be included as a covariate in longitudinal models, and the pre-specified landmark estimates at ages 5 and 10 fall wholly within the proxy-report period, allowing an interpretation that is unaffected by the transition to self-report.

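### The projected capacity of 14–24 covariates pools HD and ARM events, but the plan fits the two diseases separately, and neither model spans that range

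*Protocol article*

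**What the plan says.** All references are to the protocol article.

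- **Sample size and expected enrolment.** "Combined, the registry aims to enroll approximately 96 participants per year", and "total enrollment over 5 years is projected at 480–680 participants". The event rates come from "published ARM cohort data reporting approximately 24–30% achieving full fecal continence" and "HD cohort data reporting approximately 39% achieving a BFS ≥ 17 by adolescence". These are merged into one rate of 30–35%, giving 145–240 events, "supporting inclusion of up to 14–24 covariates in the primary Cox model at an events-per-variable (EPV) threshold of 10". The section then makes multivariable analysis conditional on confirming this threshold at interim review.
- **Statistical analysis, Objective 3.** "multivariable analyses will be conducted separately for ARM and HD rather than as a single combined model". Each disease has its own five named predictors, and each Cox model is released only when 10 events per variable (EPV) is reached within that cohort.
- **Strengths and limitations.** "the two cohorts are never pooled for primary, survival, or multivariable analysis, and the events-per-variable threshold is assessed within each cohort separately". The same paragraph calls HD the smaller cohort and accepts that its adjusted analyses may come later.
- **Study population and setting** also requires separate primary and multivariable analyses.
- **Outcome measures** refers the EPV condition for secondary outcomes back to the sample size section, not to Objective 3.

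**The concern.** The only numerical support for the primary multivariable analysis describes a single combined Cox model, which three other sections exclude. A reader planning the interim review, or judging feasibility, would credit each disease model with more capacity than it can have.

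The trigger wording is affected too. In the sample size section the threshold follows directly from the pooled count; in Objective 3 it is applied per cohort. The secondary outcomes point to the former, although one of them, Hirschsprung-associated enterocolitis, can occur only in the HD cohort.

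**Working it through.** **1. Reproduce the stated figure.**
- Enrolment: (5 + 3) × 12 = 96 per year; 96 × 5 = 480; adding a backlog of 200 gives 680.
- Events: 480 × 0.30 = 144 and 680 × 0.35 = 238, stated as 145–240.
- Capacity at EPV 10: 14.4 and 23.8, stated as 14–24.

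The arithmetic is sound, but only with both diseases in one count.

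**2. Limits that need no exact split.** The published rates are taken at face value as five-year rates.
- If every enrolee had ARM, events would be 480 × 0.24 = 115 to 680 × 0.30 = 204, a capacity of 11–20. ARM cannot span 14–24 under any split.
- If HD is the smaller cohort, its share is below one half and its events stay below 680 × 0.5 × 0.39 = 133, a capacity of at most 13.

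**3. Capacity under assumed splits.** The documents give no HD:ARM split, so the ARM share *s* is an assumption. ARM events run from 480 × *s* × 0.24 to 680 × *s* × 0.30. HD events run from 480 × (1 − *s*) × 0.39 to 680 × (1 − *s*) × 0.39. Capacity is events / 10, rounded down.

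| Assumed ARM share | ARM events | ARM capacity | HD events | HD capacity |
|---|---|---|---|---|
| 50% | 58–102 | 5–10 | 94–133 | 9–13 |
| 60% | 69–122 | 6–12 | 75–106 | 7–10 |
| 69% | 80–141 | 7–14 | 57–81 | 5–8 |
| 80% | 92–163 | 9–16 | 37–53 | 3–5 |

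The 69% row uses the incidences under Catchment and representativeness: ARM 10,000 / 2,162 = 4.63 per 10,000, HD 2.05 per 10,000; 4.63 / (4.63 + 2.05) = 0.69.

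**4. The pooled upper rate.** With ARM at 30% and HD at 39%, a combined 35% needs an HD share of (0.35 − 0.30) / (0.39 − 0.30) = 0.56. That conflicts with HD being the smaller cohort. The effect is small: at an even split the rate is 34.5%, or 680 × 0.345 = 235 events instead of 238. The lower rate of 30% needs an HD share of (0.30 − 0.24) / (0.39 − 0.24) = 0.40, which raises no conflict.

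**5. Variables against parameters.** Severity and phenotype lists 7 Krickenbeck groups (6 parameters as categories) and 4 lengths of aganglionosis (3 parameters). Assume one parameter each for age at repair, sex, syndromic status and a single linear deprivation score.
- ARM: 6 + 3 + 1 = 10 parameters, so 100 events at EPV 10.
- HD: 3 + 3 + 1 = 7 parameters, so 70 events.

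At the 69% share, the projections of 80–141 (ARM) and 57–81 (HD) straddle these needs: attainable, not assured.

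**The case against.** The strongest defence is that the rule which decides when a model is fitted is already right. Objective 3 applies EPV 10 within each cohort and otherwise restricts that cohort to descriptive and unadjusted comparisons; the limitations section repeats this and concedes delay for HD. The 14–24 figure is labelled a feasibility projection, and the registry requires no minimum sample size. This stands, and it limits the harm. It does not rescue the figure, which is still attributed to a model the plan excludes.

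A reader might infer more than the documents support:

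- **That neither model can reach 14.** ARM reaches 14 at the top of its range with a share of about 69%, and 16 at 80%. What holds is that neither model spans 14–24.
- **That the gate opens at 50 events and releases overfitted models.** This needs each of the five predictors to count once (5 × 10 = 50). The protocol does not say so.
- **That the models need still more parameters.** Material and social deprivation "will be treated as separate dimensions and analysed as quintile scores", which could mean two terms, or eight parameters if both are categorical. But Objective 3 names a single deprivation quintile, and a score suggests a linear term. Coding is properly left to an analysis plan.
- **That the Year 4 and 5 report promises models that cannot be fitted.** That report is subject to the same trigger, and the milestones are to be updated.
- **That 69/31 is the registry's case-mix.** It comes from population incidences; the registry takes tertiary referrals, a backlog and re-engaged patients.

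Some other models, such as that for loss to follow-up, list diagnosis type as a predictor. This does not bear on the primary Cox model.

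**Conclusion.** The point holds as a contradiction with a measurable size. The capacity of 14–24 is correct arithmetic for a pooled model that the plan does not fit. Per disease, it is about 5–16 for ARM and 3–13 for HD across assumed ARM shares of 50–80%, and about 7–14 and 5–8 at the incidence-based share. That neither model spans 14–24 needs only the protocol's own enrolment, its own rates and its statement that HD is the smaller cohort; the narrower ranges depend on the assumed split. The upper combined rate is also slightly too high for a registry in which HD is smaller.

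The consequence is an overstated feasibility figure and trigger wording that differs between sections. Overfitting would follow only if the gate were read as counting five predictors rather than estimated parameters.

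**What to change.** 1. In the sample size section, replace the pooled 14–24 with projected events and capacity for each cohort, under a stated HD:ARM split with a range around it. The COCOE caseload would be a better basis for the split than population incidence. Derive any combined rate from that same split.
2. Reword the trigger in the sample size section, and the cross-reference to it under Outcome measures, so that both point to the within-cohort gate of Objective 3.
3. State that EPV counts estimated parameters, so that a multi-category predictor counts for each parameter it uses. The coding itself can stay with the analysis plan.

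Collapsing categories or using a penalised model are design choices and are not needed to remove the contradiction. The cost is wording and a less favourable projection. No formal analysis has yet been done, so no result is affected.
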